### Recruitment {15}

Participants will be recruited from the general population. Information leaflets will be distributed among families by health care organizations and schools that provide care to children with ID and/or VI. The leaflet will contain contact addresses of the researchers. Social media and websites of care organizations, support groups, and parent networks will also be used to recruit participants. This includes information videos, pictures, and digital leaflets. Parents can also find more information on the Dutch webpage about the study.

## Assignment of interventions: allocation

### Sequence generation {16a}

The participants will be randomly allocated (1:1) individually to the experimental and control group using an allocation schedule. The randomization will be stratified by sibling age, including two stratification groups: siblings aged 6 and 7, and siblings aged 8 and 9. Stratification by sibling age is executed because we expect that the age of the sibling can influence the intervention effect. Next to stratification, block randomization will be used in order to ensure equal group sizes. The block sizes will be randomized as well, varying between 4, 6, and 8.

### Concealment mechanism {16b}

The allocation schedule will be produced and kept by an independent researcher. When a new participant is included, the researcher will ask the independent researcher what condition is allocated to that participant’s number. The researcher will then send an email with this information to the research assistant that will visit the participant for the assessment. The research assistant will be requested to open this email after the participant has completed the pre-test assessment.

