### Who will take informed consent? {26a}

When inclusion criteria are met, the parent will receive the participant information letter by email. A simplified child-version of the information letter will also be sent to the parent, so that the parent can discuss the research procedure with the sibling. When the parent and sibling want to participate in the study, the parent will be asked to sign and return two consent forms: one in behalf of the sibling and one for their own participation in the research. The consent form for the sibling’s participation also needs to be signed by the other parent that has custody or by the legal guardian. The signed informed consent forms can be given to the research assistant at the beginning of the pre-test assessment. The parent and child can ask questions about the study procedure to the research assistant before handing over the informed consent form. This research assistant will also sign the informed consent form in order to declare that they have fully informed the participant.

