### Participant timeline {13}

Families that show interest in participating in the study by contacting the researcher will receive the subject information letter through email. This consists of both an extensive information letter for the parent and a simplified summary for the sibling. The parent and sibling can then decide whether they want to participate in the study. When they indicate that they want to participate, the researcher will call the parent for a brief eligibility screening, to provide more information about the study procedure and to answer questions. After that the research assistant will contact the parent to plan the three home visits in which the assessments are completed. Parents are given the opportunity to choose if they want to fill out the questionnaire during the home visits or at another moment in the week prior to the visit. At the pre-test assessments, parents will hand over the informed consent forms to the research assistant prior to starting the assessment. After completing the pre-test assessments, the parent and sibling will be informed about the group they have been allocated to. The siblings in the experimental group will then play the serious game over a period of 4 weeks. The siblings in the waitlist control group can play the game after completing the follow-up assessment. A visualization of the study timeline can be found in Fig. 1.

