### Implementation {16c}

The researcher who enrols the participants will chronologically assign a number to each participant based on the moment of entry. The allocation schedule will be produced with a computerized random number generator by an independent researcher, and not be visible for the researchers.

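### The researcher who screens and enrols appears to learn each family's own arm before consent is handed over and before baseline, and the assistant's blinding at T0 rests on a request not to open an e-mail

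*Protocol article*

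**What the plan says.** The relevant steps are spread over several sections of the protocol article.

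- **Screening.** Under Participant timeline {13}, once a family says it wants to take part, "the researcher will call the parent for a brief eligibility screening".
- **Numbering.** Under Implementation {16c}: "The researcher who enrols the participants will chronologically assign a number to each participant based on the moment of entry". The same section says that an independent researcher produces the schedule, which will be computer-generated "and not be visible for the researchers".
- **Release of the arm.** Under Concealment mechanism {16b}: "When a new participant is included, the researcher will ask the independent researcher what condition is allocated" to that number. Then: "The researcher will then send an email with this information to the research assistant that will visit the participant for the assessment".
- **Safeguard for the assistant.** Same section: "The research assistant will be requested to open this email after the participant has completed the pre-test assessment".
- **Consent.** Under {26a}: "The signed informed consent forms can be given to the research assistant at the beginning of the pre-test assessment". Participant timeline {13} agrees: at the pre-test, "parents will hand over the informed consent forms to the research assistant prior to starting the assessment".
- **Blinding.** Section {17a} lists participants and research assistants as blinded at the pre-test only, and also the researchers who analyse the data. Section {17b} dismisses an unblinding procedure because participants and investigators cease to be blinded after the pre-test.

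**The concern.** Allocation should stay unknown to everyone who can influence entry or baseline until consent is complete and baseline has been recorded. Here the arm seems to reach the enrolling researcher at inclusion, and the assistant's inbox before the visit.

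Three things are at stake.

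- **The current family.** Between inclusion and the T0 visit, a member of the study team knows the arm while the family has not yet handed over consent. Reminders, scheduling or persistence could differ by arm, without any intent.
- **The baseline.** The assistant reads the questions aloud to children aged 6 to 9 and collects open-ended answers. An e-mail opened early could affect T0, which is the reference point for the intervention-by-time test.
- **Later families.** Someone who accumulates past arms in a blocked schedule can guess the next one better than by chance.

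The matter weighs more than usual because families and assistants know the arm after T0, and the outcomes are largely child- or parent-reported. Concealment up to T0 is one of the few protections against bias that this design retains.

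**Working it through.** **Order of events.** The protocol states no figure on this point, so the first check is to put the steps in sequence.

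1. The researcher screens by telephone ({13}).
2. The enrolling researcher assigns a number in order of entry ({16c}).
3. At inclusion, the researcher asks for and receives the arm for that number ({16b}).
4. The researcher e-mails the arm to the assistant who is still to visit ({16b}).
5. At the visit, consent is handed over before the assessment starts ({13}, {26a}).
6. T0 is measured.
7. The assistant opens the e-mail, and the family is told its arm ({16b}, {13}).

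The researcher knows the arm from step 3, but consent and baseline come at steps 5 and 6. No safeguard covers the researcher. The assistant's safeguard is a request, and asking for the e-mail to be opened only after the pre-test makes sense only if it can arrive earlier.

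**Consistency.** Section {17b} implies that investigators are blinded through the pre-test. Section {16b} gives the researcher the arm before it. Section {17a} does not list the enrolling researcher as blinded at all. The three sections do not describe the same procedure.

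**Predictability of later arms.** Inputs from Sequence generation {16a}: 1:1 allocation, two age strata, and block sizes varying at random between 4, 6 and 8. From Sample size {14}: 154 children. Assumptions: 154/2 = 77 per stratum, the three block sizes equally likely and known to the guesser, and a guesser who knows every earlier arm in the stratum.

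The simple rule is to guess the arm that is currently behind and toss a coin at ties. For a complete block of size 2m, the expected number of correct guesses is m + (4^m / C(2m, m) − 1)/2.

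| Block size | Expected correct | Share |
|---|---|---|
| 4 | 2 + (16/6 − 1)/2 = 2.83 | 70.8% |
| 6 | 3 + (64/20 − 1)/2 = 4.10 | 68.3% |
| 8 | 4 + (256/70 − 1)/2 = 5.33 | 66.6% |

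With equally likely sizes, the share over complete blocks is (2.83 + 4.10 + 5.33)/(4 + 6 + 8) = 12.26/18 = 68.1%. Stopping at 77, usually part-way through a block, lowers this slightly. Simulation gives 67.7% for this rule (20,000 schedules) and 67.7% for a guesser who makes optimal use of the whole history (4,000 schedules).

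In the second simulation the next arm is certain for 2.3% of participants (0.023 × 154 ≈ 3.5 children). One arm has a probability of at least 75% for about 35% of participants (0.346 × 154 ≈ 53 children). The result hardly depends on the even age split, because the per-block shares do not involve stratum size. With 30 to 124 children in a stratum, the simulated share stays between 67.5% and 68.0%.

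**The case against.** **The schedule is concealed.** An independent researcher makes and keeps it, arms are released singly for participants who are already included and numbered, and block sizes vary. Hiding the list while releasing one arm at a time is ordinary central allocation, so {16b} and {16c} do not conflict on that ground. This stands. A reader might infer that the next family's allocation is not concealed. The documents do not support that: the next arm is never disclosed and is certain for only about 2% of participants.

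**The 68% is not caused by the timing of release.** It describes permuted blocks to anyone who knows past arms, whenever they learned them. Researchers also answer questions about playing the game during the intervention weeks ({11c}), so they could learn past arms that way. This also stands. Later release alone would not bring 68% down to 50%.

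**Selection has little room to operate.** Families come forward themselves, eligibility is largely factual, and the household chooses which sibling takes part. This weakens the route to choosing the next family by expected arm. It does not remove differential follow-through with a family whose arm is already known.

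**Baseline is protected.** Assistants follow a standard protocol, are described as blinded at T0, and families learn their arm only afterwards. This is true as intended, but the means is only a request.

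**Analysis set.** A reader might infer that a family declining at the T0 visit counts as randomised and so breaks the intention-to-treat rule in {20c}. No section says so, and Table 2 places allocation in a column after consent. At most, the moment of randomisation is not pinned down here, and the full protocol may settle it.

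**Two links are inferred.** The article does not say that the researcher in {13}, {16b} and {16c} is one person, and it gives no time for the e-mail. Both are the natural reading, but neither is stated.

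**Conclusion.** The point holds for the current family. As written, the enrolling researcher most naturally learns a family's own arm before consent is handed over and before baseline, and the assistant's blinding at T0 depends on leaving an e-mail unopened. This disagrees with the implication in {17b} that investigators are blinded until after the pre-test.

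The documents give no basis for putting a size on any resulting bias. For later families the effect is partial predictability. About 68% correct guesses against 50% is an upper figure, because it requires a screener who tracks the running balance of each stratum. It would fall only as far as the enrolling researcher is also kept from learning past arms by other routes.

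This should be fixed, but it does not show that concealment of the sequence has failed. Confidence is moderate because of the two inferences named above.

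**What to change.** Change Concealment mechanism {16b} so that the independent researcher sends the arm directly to the assistant, and only after the assistant confirms that consent has been handed over and that all T0 child and parent assessments are complete. The enrolling researcher is not in that chain. State that this release is the moment of randomisation.

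Reconcile {16b}, {16c}, {17a} and {17b} with this procedure, saying who is blinded and until when. Apply it to all families still to be enrolled. To gain on predictability as well, keep the enrolling researcher from learning past arms by other routes as far as practicable, for example by having someone else answer questions about the game.

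The core change re-routes one e-mail per family and uses the independent researcher who already holds the schedule. The small cost is availability: that person must respond around the time of each visit, or the family is told its arm shortly afterwards. The optional separation of tasks would need some further staff arrangement.

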### Implementation {16c}

The researcher who enrols the participants will chronologically assign a number to each participant based on the moment of entry. The allocation schedule will be produced with a computerized random number generator by an independent researcher, and not be visible for the researchers.

## Assignment of interventions: blinding

### Who will be blinded {17a}

Participants and research assistants will only be blinded for intervention at the pre-test assessment. The researchers that execute the data analysis will be blinded for intervention. The assigned intervention will not be visible in the dataset.

### Procedure for unblinding if needed {17b}

This is not applicable, as participants and investigators are no longer blinded after pre-test assessment.

## Data collection and management

### Plans for assessment and collection of outcomes {18a}

Siblings and parents will complete 60- to 90-min assessments at pre-test (T0), post-test after 5 weeks (T1), and follow-up, 6 to 8 weeks after the post-test (T2). In total, the data collection takes 12 to 14 weeks per participant. Siblings and parents will separately fill out questionnaires on a computer or tablet using Qualtrics [68]. Some of the outcomes are measured with both parent- and child-report questionnaires, whereas other outcomes are measured with only one informant.

Research assistants will visit the participants at their homes to take all assessments following a standard protocol. These assistants are Bachelor or Master students in educational sciences at the Vrije Universiteit Amsterdam. The students will receive a 2-hour training on taking the assessments by the researcher. During the home visits, the research assistant will give instructions to the siblings and read out the questions. Parents can fill out the questionnaire without assistance during the home visit, or at another moment in the week prior to the visit. However, the research assistant can provide the parent, when needed, with an extra standard explanation about the questions.

### Plans to promote participant retention and complete follow-up {18b}

In order to promote participant retention, the research assistant will remain contact with the parent during the study period. The home visit for the follow-up assessment will already be planned at the end of the post-test assessment. This home visit can be planned within a timeframe of 3 weeks, to make it more convenient for the family to choose an appropriate moment. The research assistant will remind the parent of this home visit 1 week before it takes place. No additional outcome data will be collected from participants that no longer want to complete the assessments.

### Data management {19}

Based upon entry, a participant number will be assigned to all participants (consisting of pairs of a parent and a child) by the researcher. The key-file will contain the code, name of the parent, name of the child, email address of the parent, phone number of the parent, and address of the family. The key-file will be stored separately from the research data on a secured cloud-based shared-storage environment on the server of the Vrije Universiteit Amsterdam, and will only be accessible to the researcher, principal investigator, and monitors. The research assistants that are involved in data collection will get access for a limited time to only a personal folder on the secured storage environment where they can find the contact information and participant number of the participants they visit.

Most of the research data will be collected using the safe online survey software Qualtrics. In Qualtrics, only the participant number will be entered, there will be no data that makes direct identification of the participant possible. In addition, audio recordings and drawings are obtained. Only the participant number will be written on the drawings that the siblings will make. Digital game statistics, including the user name of the participant but no other identifying information, are obtained as well as the children play the game on a secured website on the server of the Vrije Universiteit Amsterdam. Research data will be saved encrypted and processed using an identification number on a secured cloud-based shared-storage environment on the server of the Vrije Universiteit Amsterdam with automatic back-up. Paper files will be stored in locked cabinets.

After publication, the anonymized dataset of the quantitative data will be made available upon request for future research for 15 years on an appropriate data archive. Personal data and informed consent forms will be archived in a safe depository for 15 years as well. A data management plan has been composed with assistance of a data management expert.

### Confidentiality {27}

Researchers and student who are involved in collecting and processing data will sign a nondisclosure agreement. Other persons that have access to the research data include the review committee; the security committee who monitor the data for research purposes; and the persons who check the quality of the study. These persons will also sign a nondisclosure agreement. Data will be handled confidentially and in accordance with the General Data Protection Regulation (GDPR), in order to ensure the privacy of the participants. All research data is pseudonymized.

### Plans for collection, laboratory evaluation, and storage of biological specimens for genetic or molecular analysis in this trial/future use {33}

No biological specimens are collected in this study.

## Statistical methods

### Statistical methods for primary and secondary outcomes {20a}

In the current study, quantitative data will be analyzed using IBM SPSS Statistics 27 [69], and qualitative data will be analyzed using ATLAS.ti. 22 [70].

The primary and secondary objectives, as well as the exploratory analysis on parenting self-efficacy, will be answered by computing the linear mixed-effects model procedure (MIXED). To test the effect of the intervention, the main effects of intervention and time, together with the interaction effect between intervention and time, will be included in the model. The primary objectives will be analyzed multivariate, whereas the secondary objectives are analyzed univariate. For the latter, the Bonferroni correction will be used to determine the alpha level. Child-report and parent-report outcomes will be analyzed separately. Cohen’s Ds will be calculated to determine the effect size. The answers to the open-ended questions will be analyzed using thematic coding with conventional qualitative content analysis [71]. The outcomes of the PAIR will be analyzed in both a quantitative way using the manual [48]. Thematic analysis of the drawings will also be executed according to the procedure described in Guidotti et al. [49]. The drawings of the PAIR are scored by two independent researchers. Intra-class correlations will be calculated to assess the inter-rater reliability.

For social validity, the mean scores will be reported. Additionally, one sample *t*-tests will be executed in order to test if the mean score significantly differs from the neutral score (3). Conventional qualitative content analysis will be used to analyze the answers to the open-ended evaluation questions [71].

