### Sample size {14}

Using GLIMMPSE 3.0 [63], the required sample size to conduct multivariate linear mixed models for the primary outcomes quality of life and sibling adjustment to the disability of the brother or sister is calculated. The sample size is estimated with an alpha of 0.05 and a target power of 0.80 and is based on an interaction effect hypothesis, including between (intervention) and within (measurement point) variance. Correlations between measurement points are estimated to be 0.60 (T0–T1; T1–T2) and 0.40 (T0–T2), based on previously found test-retest correlations on the PedsQL [64]. The correlation between the outcomes is estimated to be 0.30. This estimate is based on a previously found correlation between the SPQ and a measure of wellbeing and adjustment (Strengths and Difficulties Questionnaire; SDQ), as no information about the correlation between de SPQ and a measure of quality of life was available [65]. A scale factor of 1.2 for variability is inserted in the sample size calculation, in order to be more conservative.

For both quality of life and sibling adjustment to the disability of the brother or sister the child-report means and standard deviations from previous sibling studies are used [41, 66]. For the control group, no change is expected on the outcome measures. For the intervention group, change is expected gradually. The expected total change (at T2) on quality of life is based on the Minimal Clinically Important Difference [67]. The expected total change on sibling adjustment to the disability of the brother or sister is based on the measured change in a previous sibling intervention study [41]. No change in standard deviations is expected on all measurement points.

The computed sample size calculation based on the beforementioned parameters results in a required sample size of 134, with 67 participants in the intervention group and 67 participants in the waitlist control group. Based on two previous intervention studies [22, 29], a dropout rate of 15% is accounted for. The total required sample size is therefore 154. This includes 154 siblings and their 154 parents.

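### The primary model tests change from T0 with a free T0 group difference; at the protocol's own correlations this gives up about 30% of the information that baseline adjustment would keep

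*Protocol article*

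**What the plan says.** The section Statistical methods for primary and secondary outcomes {20a} specifies a linear mixed model in SPSS in which "the main effects of intervention and time, together with the interaction effect between intervention and time, will be included in the model". It names no baseline covariate and no constraint on the T0 means. The primary outcomes are analysed jointly and the secondary outcomes one at a time.

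Sample size {14} uses the same test: the calculation "is based on an interaction effect hypothesis, including between (intervention) and within (measurement point) variance". The time points are T0, T1 and T2, so T0 is a response and not a covariate. The section adds that "Correlations between measurement points are estimated to be 0.60" for T0–T1 and T1–T2, and 0.40 for T0–T2. Standard deviations are taken as constant over time. For the effect pattern, "For the control group, no change is expected on the outcome measures", and the intervention arm is expected to change gradually up to T2.

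The section on additional analyses {20b} adjusts for a baseline variable only if the arms differ significantly on it and it is also associated with the outcome.

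**The concern.** When T0 is a response and the model has an intervention main effect, the arms may differ at T0 by any amount. The intervention-by-time terms then measure the difference between arms in change from T0. This gives the T0 score a fixed coefficient of one, whatever its actual correlation with the later score. At correlations of 0.60 and 0.40 that coefficient is too large. A chance imbalance at T0 is over-corrected, and noise from T0 is carried into the treatment contrast.

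Nothing is gained in return. Allocation is random, and the protocol has it revealed only after the pre-test, so the true T0 difference is zero by design and need not be estimated. The consequence is wider intervals and lower power, on every outcome analysed this way, than the data already being collected could give.

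**Working it through.** **Inputs.** From Sample size {14}: correlations 0.60 (T0–T1, T1–T2) and 0.40 (T0–T2), constant SD, correlation of 0.30 between the two primary outcomes, variance scale factor 1.2, alpha 0.05, power 0.80, N = 134 (67 per arm). Three assumptions are added: a two-sided or F test, complete data, and half of the total effect present at T1 as a reading of gradual change. Other splits are shown below.

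**The plan's own figure.** The 134 cannot be rebuilt from the article, because the means, SDs and target changes are only cited. It is taken as given, that is, 0.80 power at N = 134 for the planned test. The comparison below does not need those values. The 1.2 factor and the 0.30 correlation cancel in the ratio.

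**Single time point** (variance per child, in units of σ²). Change from T0 has variance 2(1 − r). Baseline-adjusted, it is 1 − r². The ratio is (1 + r)/2.

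- T2, r = 0.40: 2(0.60) = 1.20 against 1 − 0.16 = 0.84. Ratio 0.70, so 30% is lost. Ignoring T0 altogether gives 1.00, so change is noisier than not using T0 at all.
- T1, r = 0.60: 2(0.40) = 0.80 against 1 − 0.36 = 0.64. Ratio 0.80, so 20% is lost.

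**Joint test of T1 and T2.** The covariance of the two contrasts is:

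- free T0 difference: variances 0.80 and 1.20, covariance 1 − 0.60 − 0.40 + 0.60 = 0.60
- T0 means equal, or T0 as covariate: variances 0.64 and 0.84, covariance 0.60 − 0.60 × 0.40 = 0.36

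Let s be the share of the effect present at T1, so the effect vector is d = (s, 1). The noncentrality is proportional to d′V⁻¹d:

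- free: 2s² − 2s + 1.333
- constrained: 2.059s² − 1.765s + 1.569

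| Effect at T1, T2 | Free | Constrained | Information lost |
|---|---|---|---|
| 1/3, 1 | 0.889 | 1.209 | 26% |
| 1/2, 1 | 0.833 | 1.201 | 31% |
| 2/3, 1 | 0.889 | 1.307 | 32% |
| 1, 1 | 1.333 | 1.863 | 28% |
| 0, 1 (T2 only) | 1.333 | 1.569 | 15% |
| 1, 0 (T1 only) | 2.000 | 2.059 | 3% |

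For the half-at-T1 pattern the gain is 1.201/0.833 = 1.44, equivalent to 44% more children. With the full effect from T1 it is 1.863/1.333 = 1.40. Putting both outcomes in the model with correlation 0.30 leaves the ratio unchanged (0.694).

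**Power at N = 134.** Two outcomes times two contrasts give 4 degrees of freedom. The noncentrality that yields 0.80 power is 12.38. Under the constrained model it becomes 12.38/0.694 = 17.84, which gives power 0.932 (0.926 for the corresponding 2-df test of one outcome). Equal 0.80 power would need about 94 children instead of 134. For a single T2 contrast, 0.80 becomes 0.92, or 47 per arm instead of 67.

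**The case against.** The strongest reply is that nothing here is in error. The interaction model is standard and unbiased under randomisation, and it is the test the trial was sized on. By its own plan the trial has its 0.80 power. All of that is true, and it makes this a matter of efficiency and not of validity.

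The size also depends on the effect pattern. With an effect only at T2 the joint test loses 15%, and with an effect only at T1 it loses 3%. The half-at-T1 split is an assumption. Patterns that do fit gradual change, with one third to all of the effect at T1, lose 26% to 32%. The correlations come from test-retest data on the quality-of-life scale, so the loss on the other scales is unknown. The single-contrast loss is (1 − r)/2, for example 15% at r = 0.7 and 10% at r = 0.8. The direction is the same for any r below 1.

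Three further objections do not stand.

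- **Baseline is already handled in {20b}.** That adjustment depends on a significant imbalance. Under randomisation, a test at the 5% level triggers it for a given outcome about 5% of the time, so the efficiency is usually forgone and the final model depends on the data.
- **Equal T0 means could fail if a research assistant opened the allocation email before the pre-test.** This is speculation, and a T0 score disturbed in that way would bias change scores too.
- **Using T0 as a covariate drops children seen only at T0, against the intention-to-treat rule.** With T0 recorded for everyone, those children carry no information on the treatment effect at T1 or T2 under either form, and the estimate is the same.

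**Conclusion.** The concern holds. At the protocol's stated correlations and constant SD, the planned contrast discards 30% of the available information at T2 and 20% at T1. For the joint test, the loss is 26% to 32% across effect patterns that fit gradual change. At N = 134 that is the difference between 0.80 and about 0.93 power if half the effect is present at T1. The figures rest on the planning correlations and complete data. For scales without a stated correlation only the direction is certain. The planned analysis remains valid, so this is an improvement worth making and not the correction of a bias.

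**What to change.** Make a constrained longitudinal model the primary analysis. Keep T0, T1 and T2 as responses with an unstructured covariance, include time, omit any intervention effect at T0, and estimate the group difference at T1 and T2 for each outcome. In SPSS MIXED this is a treatment indicator that equals 1 only for the intervention arm at T1 and T2, crossed with time, in place of the intervention main effect.

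An equivalent form takes T1 and T2 as responses, with T0 and T0-by-time as covariates. In the joint model of the two primary outcomes, let both T0 scores enter for each outcome if the covariance is left fully unstructured.

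Use the same form for the secondary outcomes and parenting self-efficacy. For T0 scores of the outcomes it replaces the significance-triggered adjustment in {20b}. Keep the planned interaction model as a sensitivity analysis.

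The cost is a change of model wording. No new data, visits or children are needed, and the sample size target can stay as it is.
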